#### Text Messaging

Between home visits, HCs will communicate with patients through telephone calls and text messaging. All text messages will be tailored by HCs and sent through a custom software app (*mytapp*). We developed *mytapp* for community-based health behavior research. *mytapp* sends messages immediately or at a scheduled date or time, recurrent messages (daily, weekly, or weekdays), group messages, or multiple question surveys. HCs receive training on *mytapp* and schedule messages for their patients regarding appointments and medications. HCs send messages to maintain motivation, elicit feedback on progress, and screen for barriers that may reduce the chance of success (Table 1). For example, a morning text message may ask a patient how they did on their goal the previous day.

No more than 7 messages are delivered weekly, except for optional medication reminders. For safety, patients are reminded that text messages are sent in an automated fashion by a computer. Furthermore, they are reminded that urgent health questions should be directed to their PCP and not sent in a text message. HCs monitor patient responses through their study phones.

Texts are monitored by the HCs with additional oversight by the project coordinator.

**Table 1 table1:** Example text message templates.

Message type	Example
Medication reminder	“Hi, [name], just checking to see if you took your morning pills.”
Refill reminder	“Make sure you don't run out. Check to see when a pill refill is due.”
Appointment reminder	“Just a reminder that you have a doc’s appointment today.”
Goal monitoring	“Remember your goal. Did you take your meds last night?”
Glucose monitoring	“Hello, [name], have you had time to check your sugar today?”
Self-efficacy	“Taking your meds is within your control. You can do it.”
Motivation	“You have come a long way! Keep up the good work!”

#### Usual Care

All participants spend 1 year in the usual care condition, either year 1 or 2, depending on the randomization. During receipt of usual care, they receive health care from their usual providers without the support of a pharmacist or HC. There are no home visits or pharmacist telehealth videoconferencing encounters with usual care. In addition, participants receive a 1-page list of clinic resources with names and direct telephone numbers (eg, social worker or clinical pharmacist) along with a low-literacy, paper-based diabetes education pamphlet [87]. Usual care reflects the type of health care that patients receive outside of any participation in research.

#### Intervention Fidelity

To continuously evaluate the fidelity of both conditions, we review logs maintained by the HCs weekly, including visit dates, length of visits, visit content, and disposition (eg, visit completed, and patient unreachable). Weekly group meetings with HCs and the research team provide an opportunity to monitor intervention delivery. Monthly lunch meetings with clinical pharmacists, HCs, and investigators ensure active collaboration between HCs and pharmacists. All technology-related difficulties are reported to the coordinator immediately and discussed in weekly meetings with the investigators. One investigator, a health psychologist, maintains weekly contact with HCs to provide emotional support and incorporate structured training opportunities. Text messages sent and received via *mytapp* are reviewed monthly.

#### Data Collection

Trained, blinded RAs collect physiological and self-report data through interview administration within the clinical research center at UI Health at 5 time points: baseline and every 6 months for 2 years. RAs are matched to patient language preferences in English or Spanish. Laminated cards with Likert-type scale responses are provided as a visual reference to the patients. Interview data are entered directly into laptop computers using Research Electronic Data Capture (Vanderbilt University) electronic data capture web application [88]. The baseline survey requires an average duration of 60 minutes with subsequent follow-up visits lasting 30 minutes. Subjects receive US $30 as compensation for travel and time at each of the 5 data collection points (plus US $50 if at least one videoconference is completed in the prior 6 months during the intervention period). Public transit cards and parking passes are provided when needed. Participants are informed of their randomization assignment at the end of the baseline data collection.

Sociodemographics include age, gender, self-reported race and ethnicity, country of origin, income, highest level of education, employment status, global health status [89], and insurance. Diabetes and medical history include self-reported time since diabetes diagnosis, prior receipt of diabetes education, current therapy, known diabetes complications, and comorbid conditions. Health literacy is assessed using 3 screening questions with high discriminatory power among English- and Spanish-speaking populations [67,90,91]. Mobile phone use and comfort sending text messages is also assessed using 5 items [68].

Intermediate variables are also collected at each of the 5 time points. Perceived severity of diabetes and perceived susceptibility are assessed using 2 items adapted from the study by Bradley et al [92]. The perceived benefits of therapy are measured by a 5-item survey related to the benefits of therapy [71]. Diabetes distress is measured using the brief Diabetes Distress Scale [73]. Depression is measured using the Patient Health Questionnaire [75,76]. Social support is measured using an assessment of the amount of total support received and satisfaction with support from family, friends, and the health care team [93]. Self-efficacy is measured using the Stanford 8-item self-efficacy for diabetes survey [94]. Contextual data include an environmental survey that addresses loneliness, social cohesion, and neighborhood safety as well as the identification of stressful life events [95-97].

HCs record the dates of patient contacts in REDCap (eg, phone calls and home encounters). Clinical progress notes are completed in the EMR after every participant contact (by phone if longer than 15 minutes and in-person). Information includes mode, time, location (home vs clinic), content of contact, results of glucose or blood pressure self-monitoring, goals, life events, pharmacist interactions, and interventions. Intensification of therapy will be defined as the number of dosage increases of antihypertensive, hypoglycemic agent, or insulin or the addition of a new agent since the baseline visit [98-100]. Chart review will define the number of PCP visits and pharmacist videoconferences as well as the number of pharmacist- or physician-initiated medication changes.

*Physiologic outcomes* will be collected at 5 time points (0, 6, 12, 18, and 24 months). The research staff will perform phlebotomy, blood pressure, weight, and height recordings. HbA_1c_ and fasting lipid profile (total cholesterol, high-density lipoprotein, LDL, and triglycerides) are obtained via phlebotomy. A calibrated digital scale measures weight. A height stadiometer measures height, with subjects removing their shoes (for BMI assessment). Blood pressure is assessed in subjects sitting down for at least 5 minutes, following a standard procedure. Health-related quality of life is measured using the EuroQol Group 5D and Diabetes Distress Scale [73].

The revised Summary of Diabetes Self-Care Activities Measure captures basic diet, exercise, blood sugar testing, foot care, and smoking with 11 core items [101]. Additional questions address skipping medications and insulin injections to evaluate adherence, as well as taking aspirin regularly. Alcohol misuse is assessed using the Alcohol Use Disorder Identification Test—Concise [102].

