**Figure 1 figure1:**
[figure not shown]
Randomized crossover study design.

The primary outcome is the change in HbA_1c_ level. Secondary outcomes include changes in blood pressure and LDL cholesterol levels. Using a 1:1 ratio, we will randomize 220 patients to either (1) a mHealth intervention delivered by a clinical pharmacist and HC for 1 year, followed by usual care for 1 year, or (2) usual care for 1 year, followed by the mHealth intervention for 1 year. Both groups will crossover at the end of year 1, such that those receiving the mHealth intervention during the first year will receive usual care during the second year (to evaluate potential maintenance of outcome improvement). Similarly, those with usual care in year 1 will crossover to receive the intervention in year 2 (to ensure that all subjects are able to receive the intervention). Of note, we do not consider HbA_1c_ levels collected at the end of year 1 when crossover occurs. The treatment received by patients (intervention or usual care) will change at the end of year 1, independent of HbA_1c_ levels.

Separate randomization schedules generated in REDCap will be used for each of the 4 main clinical sites with stratification for ethnic group (African-American and Latino) and gender to balance the proportion of participants across randomized conditions. All study procedures have been approved by the University of Illinois at Chicago Institutional Review Board (IRB 2016-0380).

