Pharmacist services are based on a standardized pharmacist management protocol. After the initial medication reconciliation, follow-up pharmacist activities include reviewing home glucose and/or blood pressure, monitoring log data obtained by the HC during home visits, identifying therapeutic goals for HbA_1c_ and blood pressure collaboratively with patients’ primary care providers (PCPs), formulating an approved plan of care, assessing changes in medications, and documenting the plan in the EMR. In addition, pharmacists provide education related to medication (name and purpose of medications and time, strength, and method of administration); drug interactions and side effects; goals of therapy; basic lifestyle modifications; and use of pillboxes, low-literacy visual medication lists, or other adherence aids. Pharmacists educate and encourage lifestyle changes, consistent with the published guidelines [67-69]. They propose medication changes based on algorithms and protocols derived from national guidelines under physician guidance [70-72]. Pharmacists routinely monitor hypoglycemic events, address prevention, and review treatments. This includes 3 steps: (1) addressing hypoglycemia with every patient contact, (2) applying principles of appropriate therapy (education, empowerment, frequent glucose self-monitoring, flexible medication regimen, individualized goals, and professional guidance), and (3) considering risk factors for hypoglycemia. Overall, there is mixed evidence regarding the benefits of aggressive glycemic control [73-75]. In the proposed study, PCPs and pharmacists adopt the American Diabetes Association approach to individualized care, where the general goal for nonpregnant adults is HbA_1c_ less than 7%. They may decide upon less stringent goals for those with a history of severe hypoglycemia, limited life expectancy, advanced complications, or extensive comorbid conditions [76]. In addition, pharmacists follow the 2018 American College of Cardiology or American Heart Association guidelines for lipid management (eg, calculating 10 year atherosclerotic cardiovascular risk to determine statin intensity) [77].

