#### HC

HCs will introduce themselves to the patients in person at the data collection visit that aligns with the beginning of the patients’ intervention year (ie, baseline visit or crossover visit at the beginning of year 2 depending on randomization). When possible, the first home visit will be scheduled at the initial introductory meeting. If this is not possible, the HC will follow up by telephone within 1 week to schedule the first home visit. All HCs are either African-American or bilingual or bicultural Latino and work with patients who are concordant for race or ethnicity and language. The HCs have an undergraduate college degree in or related to community health with experience conducting home visits. Specific training for the research study includes 80 hours of standardized HC training or retraining. As outlined in Textbox 2, training begins with an overview of the research protocol and discussion of the HC goals. The fundamental components of providing health support to marginalized populations are addressed with the required reading materials, didactic presentations, and discussions [78].

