Exploratory subgroup analyses will follow a heterogeneity in treatment effects framework [113,114]. We will determine which subjects in the intervention group had the greatest improvement in outcomes, based on multiple prespecified patient characteristics, including race (African-American or Latino), depression, comorbidities, baseline behaviors, health literacy, continuity of care, and social support. These analyses will also consider additional comparisons between subjects above and below the median levels of videoconferencing and text messaging activity. Statistical tests will be implemented as interactions within the full data set.

If the intervention results in improved HbA_1c_ more than that in the usual care, we will examine whether changes in self-efficacy, health beliefs, or social support serve as mediators for improved outcomes. In addition, we will explore diabetes-related behaviors as well as medication treatment intensification as mediators using MPlus [115-118]. To further identify the relative contributions of videoconferencing and/or text messaging, we will conduct meditational modeling with videoconferencing time, number of text messages, and HC contact time as mediating variables. This may describe any dose-response relationship between mHealth utilization and outcomes. We will compute bias-corrected bootstrap standard errors using MPlus. This offers accurate confidence intervals for mediation coefficients [119]. Due to anticipated relationships between HC activity level and mHealth delivery, we plan to inspect correlations between mediators and incorporate any significant findings in model development. This analysis will demonstrate whether the intervention effects are sensitive to mediators. Finally, given the sample size, observed (rather than latent) variables will be used in the mediation models. To enhance the power of mediation modeling, we adopt an α=.10 type I error criterion to improve the chances of finding promising mediators for future studies.

We expect a limited amount of decline in physiologic outcomes with the transition back to usual care. We will test the hypothesis that improvements in HbA_1c_ (primary outcome), blood pressure, and LDL cholesterol (secondary outcomes) will be maintained during the maintenance period. The analyses will be conducted in a manner similar to our primary hypothesis and will evaluate changes in the initial intervention group 1 year after intervention completion.

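### The therapy-intensification mediator for HbA1c counts antihypertensive changes together with glucose-lowering ones; the HbA1c mediation model should use the glucose-lowering count only

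*Protocol article*

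**What the plan says.** Methods, Data Collection, gives the only definition of intensification: the "number of dosage increases of antihypertensive, hypoglycemic agent, or insulin or the addition of a new agent since the baseline visit". It has one time origin, the baseline visit. The added-agent part carries no limit on drug class. The same paragraph plans a chart review that counts medication changes initiated by pharmacists or physicians, also without a split by class or by year.

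Methods, Data Management and Analysis, makes mediation conditional on the primary outcome. The sentence begins "If the intervention results in improved HbA_1c_ more than that in the usual care, we will examine whether changes in self-efficacy" and goes on to name further psychosocial measures as candidate mediators. The section then adds: "we will explore diabetes-related behaviors as well as medication treatment intensification as mediators using MPlus". The error rate is relaxed on purpose: "we adopt an α=.10 type I error criterion to improve the chances of finding promising mediators for future studies". The text does not say which drug classes enter the HbA1c model, or which study year the model covers.

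On timing, Study Design states: "Both groups will crossover at the end of year 1". The HC section treats the start of each arm's intervention year as two different visits, "baseline visit or crossover visit at the beginning of year 2 depending on randomization", so a count since the baseline visit does not restart at crossover.

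**The concern.** A mediator should measure the route by which the intervention is thought to move the outcome. For HbA1c, the drug route is a change in glucose-lowering therapy. Pharmacists in this trial work on both glucose and blood-pressure goals, so antihypertensive changes will be common and may differ by arm. Added to the count, they have two effects:

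- They dilute the HbA1c change associated with each counted step.
- They make the arm-to-mediator difference partly a difference in blood-pressure treatment.

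At stake is how the mediation result is interpreted. The alpha of .10 was chosen to gain power for mediators, and a pooled count gives some of that power back. This is a definition that the article states, and it does not fit the use that the article gives it. It is not a detail left for later.

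A second issue is conditional. If year-2 data enter a mediation model, a count running from baseline mixes changes made under both conditions.

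**Working it through.** The plan states no figure for this variable, so there is nothing to reproduce. The size of the problem can be shown only under assumed rates.

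**Inputs (assumptions unless marked).**
- 200 patients analysed, 100 per arm. This is close to 90% of 221 = 199, using the retention and enrolment in Results.
- Mean glucose-lowering changes in year 1: 1.6 (intervention) v 0.8 (usual care).
- Mean antihypertensive changes: 1.0 v 0.6 in the base case.
- Poisson counts, independent given arm.
- True HbA1c effect: -0.30 points per glucose-lowering change and zero per antihypertensive change. Residual SD 1.6.
- Two-sided alpha .10 (Data Management and Analysis).

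**Step 1: per-step coefficient.** With arm in the model, the expected slope on the pooled count is the true slope times the glucose-lowering share of the within-arm variance. For Poisson counts the variance equals the mean.
- Glucose-lowering: (1.6 + 0.8)/2 = 1.2.
- Antihypertensive: (1.0 + 0.6)/2 = 0.8.
- Pooled slope: -0.30 × 1.2/(1.2 + 0.8) = -0.18, which is 40% attenuation.

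**Step 2: indirect effect** (arm difference in the mediator × slope).
- Glucose-lowering only: 0.8 × -0.30 = -0.24.
- Pooled, base case: (0.8 + 0.4) × -0.18 = -0.216, a loss of 10%. The larger arm difference offsets most of the smaller slope.
- Pooled, antihypertensive mean 0.8 in both arms: 0.8 × -0.18 = -0.144, a loss of 40%.

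**Step 3: power for the mediator-to-HbA1c path**, by simulation (6,000 trials per row, regression of HbA1c change on arm and count). The glucose-only count gave 88% in every row.

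| Antihypertensive means (intervention v usual care) | Pooled slope | Indirect effect | Power, pooled |
|---|---|---|---|
| 1.0 v 0.6 | -0.18 | -0.22 | 72% |
| 0.8 v 0.8 | -0.18 | -0.14 | 70% |
| 0.6 v 0.6 | -0.20 | -0.16 | 75% |
| 1.0 v 1.0 | -0.16 | -0.13 | 67% |

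**Step 4: relax independence.** Give each patient a gamma factor with mean 1 that multiplies both rates, as engagement or visit frequency might. With the base-case means:
- Factor variance 0.5: power 97% (glucose only) v 93% (pooled).
- Factor variance 1.0: power 99% v 98%.

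The loss is then about 1 to 5 points. The pooled slope stays at -0.18, so the shared factor restores power but not the coefficient.

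**Step 5: time origin.** Let I and U be the expected yearly counts under intervention and usual care, with no carry-over.
- Month 12, count from baseline: I - U.
- Month 24, count from baseline: (I + U) - (U + I) = 0, whatever the rates.
- Year 2, count restarted at crossover (intervention-first minus usual-care-first): U - I.

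With U = 1 and I = 1.5, 2 or 3, the month-12 difference is +0.5, +1.0 or +2.0. The month-24 difference from baseline is 0 each time. The restarted year-2 difference is -0.5, -1.0 or -2.0.

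**The case against.** The strongest reply has four parts.

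**The per-step figure overstates the harm.** Mediation is judged on the indirect effect, and pooling also widens the arm difference in the mediator. In the base case only 10% of the indirect effect is lost. This stands for that scenario, but the loss is 33% to 45% when antihypertensive changes do not differ by arm (table, last three rows). A reader might infer that the trial would wrongly conclude that drug intensification did not explain an HbA1c benefit. The documents give no rates that would support so firm a statement.

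**The power loss rests on independent counts.** The same pharmacist contacts cover both glucose and blood pressure, so a shared patient factor is plausible and makes the loss small. This stands, and the independent case should be read as the unfavourable end.

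**The text never says that the classes are summed.** Separate counts per class are a possible reading, and the article's example of intensification elsewhere is starting insulin. But the definition gives a single number over a list of classes, and nothing restricts it for the HbA1c model. One pooled count remains the natural reading.

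**The baseline origin is right for year 1.** The article does not say that months 12 to 24 enter the mediation model. Data Collection also states that "Intermediate variables are also collected at each of the 5 time points"; if the count is recorded at each visit, a year-2 value is a simple subtraction. A reader might infer that the mediator is already wrong for year 2, but the documents support only a conditional caution.

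A reader might also object that dose increases of lipid drugs are not counted, although LDL is a secondary outcome and "pharmacists follow the 2018 American College of Cardiology or American Heart Association guidelines for lipid management". That does not bear on this point: the stated mediation is for HbA1c, and no LDL mediation model is described.

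**Conclusion.** The point holds as a small misspecification in an exploratory analysis. The stated definition puts antihypertensive changes into a mediator meant to explain an HbA1c effect, and the glucose-lowering subset is the better variable.

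The direction does not depend on the assumed rates, provided that antihypertensive changes do not themselves lower HbA1c. The size does:
- about 40% off the per-step coefficient;
- about 10% to 40% off the indirect effect, depending mainly on whether antihypertensive changes differ by arm;
- a power loss for the mediator path of roughly 17 points with independent counts, but only about 1 to 5 points with a shared patient factor.

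The year-2 issue arises only if months 12 to 24 enter a mediation model. The primary HbA1c comparison and the secondary treatment comparisons are untouched.

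**What to change.** In the HbA1c mediation model, define intensification as the count of glucose-lowering drug changes only: dose increases and added agents, including insulin. State that added agents count only if they are glucose-lowering.

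State which months the mediation model covers. If months 12 to 24 enter any such model, count from the crossover visit, or use the month-24 value minus the month-12 value.

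The cost is coding each medication change from the planned chart review by drug class and date. No new visits, no change to care and no change to the primary analysis are needed. Fixing the definition before the mediation analysis is run also avoids choosing it after seeing the results.
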